## Background

The Parkinson’s disease (PD) population is mainly sedentary, causing a dramatic reduction of physical activity compared to healthy older adults, even early in the disease [1, 2]. As PD progresses, falls are often harmful and very common [3]. Approximately 40–70% of people with PD fall each year, and one-third fall repeatedly [3, 4]. twice as likely as the healthy elderly population [5]. Evidence shows that falls significantly impact people’s lives with PD, including debilitating effects on confidence, decreased activity levels, and reduced quality of life [6–8]. Consequently, repeat falls are a risk factor that implies subsequent falls, often with such consequences as fractures, prolonged immobility and dependency, social isolation, and financially costly individuals and healthcare systems [9].

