### Study population

We will invite non-demented, ambulatory patients aged > 18 years old, with established idiopathic PD based on the MDS-criteria [22, 23], with a medium-high risk of falling established by a history of at least one fall in the previous 12 months with a Hoehn & Yahr (HY) stage < 3 [24], a Montreal Cognitive Assessment (MoCA) score > 18 [25], without access to non-pharmacological therapies, and one of the two additional criteria including the presence of freezing of gait (FOG) or self-selected gait speed < 1.1 meters/second [26]. We will exclude patients with severe psychiatric or cerebrovascular diseases, severe traumatic head injuries, severe orthopedic lower limb or spine problems, peripheral neuropathy, rheumatological disease, or other systemic diseases or sensory deficiencies that, according to the investigator’s judgment, may interfere with the study.

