### In-office visits (best standard medical care)

Patients will be evaluated in-office at baseline, four months, and eight months. At baseline, we will collect information on socio-demographics (age, gender, education background, living status (urban vs. rural, alone vs. with family), and PD clinical characteristics (PD duration, drugs). In each in-office visit, we will perform a complete physical and neurological exam and will complete a standard PD follow-up visit. Consensus-based clinical practice recommendations for the examination and management of falls in patients with PD will be assessed [27]. We will evaluate vital signs (standing and lying down blood pressure), heart pulse, oximetry, falls history (number, characteristics, place), visual acuity (eye chart), nutritional and dysphagia screening, balance, and strength by dynamometry. Fall prevention will be performed by providing pharmacological and non-pharmacological therapy adjustments, education, nutritional interventions, and referrals to other physicians if needed (Fig 2).

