## Statistical analysis

### Sample size

We calculated the sample size using the Epidat^®^ 4.1 statistical software. Considering that a 50% fall reduction in the number of falls compared to baseline will be obtained in 24% of the participants in the intervention group and 2% in the control group, we estimated that 70 patients (35 per group) would provide 80% power (5% probability of type 1 error) with a confidence level of 95%. By assuming a 9% dropout rate, a total sample of 76 patients will be then included in this study.

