### Outcome measures

The study’s primary outcome measure will be the total number of falls in the 4-month (short-term benefit) and 8-month (long-term benefit) after randomization. A fall will be defined as unintentionally coming to rest on the ground or other lower surface without overwhelming external force or a major internal event [56].

Other secondary outcome measures will include: 1) Cost-effectiveness, which will be estimated using natural units of health outcomes, including the incremental cost-effectiveness ratio per fall prevented and cost per extra person avoiding mobility deterioration (identified as an average number of daily steps assessed by wearable sensors); 2) A cost-utility analysis using the EuroQoL will estimate the incremental cost per quality-adjusted life-years (QALY) gain; 3) Short and long-term rate of change from baseline to four and eight months, respectively of motor, NMS, gait, balance, HR-QoL, caregiver burden, and comorbidities severity; 4) Feasibility (completed telemedicine visits) and adherence (dropout rate of telemedicine visits).

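### The 50% fall-reduction responder has no fixed baseline window, and the 2% control response behind the stated 80% power is not credible without justification

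*Protocol article*

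**What the plan says.** All references are to the protocol article.

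- **Sample size.** The trial is sized on a responder: "a 50% fall reduction in the number of falls compared to baseline will be obtained in 24% of the participants in the intervention group", compared with "2% in the control group". From this it concludes that "70 patients (35 per group) would provide 80% power" and, after 9% dropout, includes 76. No source is given for either percentage.
- **Statistical analysis.** A yes/no 50% reduction in the incidence of falls is the dependent variable of the logistic model, the only model named for falls. Neither the time point nor the baseline window is given.
- **Specific goals.** The first objective is a reduction in fall incidence, glossed as the total number of falls from baseline.
- **Outcome measures.** The primary outcome is "the total number of falls in the 4-month (short-term benefit) and 8-month (long-term benefit) after randomization".
- **Study population.** Entry requires "a history of at least one fall in the previous 12 months". This is the only dated fall window before randomisation.
- **In-office visits.** A falls history is taken at baseline, 4 and 8 months, with no look-back period stated. This care goes to both groups: "Fall prevention will be performed by providing pharmacological and non-pharmacological therapy adjustments, education, nutritional interventions".

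**The concern.** A percentage reduction in a count means something only if the two counts cover equal time or are converted to rates. Here the one dated baseline period is three times the first follow-up period and one and a half times the second, and nothing in the article says that the periods are matched or rescaled.

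There is a second problem, independent of the windows. Fall counts are small and vary by chance, and patients are selected for having fallen. Someone who enters with one fall and then has none shows a 100% reduction with no change in underlying risk. A control response near zero is therefore hard to reconcile with the plan's own eligibility rule and outcome.

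The stake is power. A 22-point difference is easiest to detect when one proportion is close to zero. If the control response is higher, the same difference needs many more patients, and the logistic model would be analysing a responder variable driven largely by chance.

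**Working it through.** **1. The plan's own figure.** Inputs from Sample size: 24% and 2%, 1:1, alpha 5% (two-sided assumed), power 80%. Mean proportion (0.24 + 0.02)/2 = 0.13.

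n per group = [1.96·√(2·0.13·0.87) + 0.842·√(0.24·0.76 + 0.02·0.98)]² / 0.22² = 1.310²/0.0484 ≈ 35.5, so 36 against the stated 35. Power at 35 per group is 79.4%. Dropout: 70/0.91 = 76.9, so 77 against 76. The arithmetic reproduces within rounding; the question is the input.

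**2. Window length alone, unchanged rate, raw 12-month baseline.**

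- 4 months: expected ratio 4/12 = 33%, an apparent 67% reduction. This passes the 50% threshold.
- 8 months: expected ratio 8/12 = 67%, an apparent 33% reduction. This does not pass by window length alone.

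**3. A floor from fall-free patients.** Against a 12-month baseline of at least one fall, zero falls in follow-up is always a response, raw or annualised. With Poisson counts at x falls per year, P(no fall) is exp(−x/3) over 4 months and exp(−2x/3) over 8. Setting each to 0.02 gives x = 11.7 and x = 5.9. These are the lowest average rates at which the floor can fall to 2%; if patients differ in their rates, the average must be higher.

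**4. Simulated response with no change in rate.** One million patients per scenario, at least one fall in the previous 12 months, and Poisson or gamma-Poisson counts (shape 1 or 0.5). A responder has a follow-up count at or below half the baseline. The article gives no fall rate, so means of 1.2–24 falls per year are an assumption. In the equal-window rows, patients with no fall in the shorter baseline window count as non-responders.

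| Comparison | Responders with no change |
|---|---|
| 12-month count vs 4-month count, raw | 75–87% |
| 12-month count vs 8-month count, raw | 21–63% |
| 12-month rate vs 4-month rate | 8–67% |
| 12-month rate vs 8-month rate | 3–51% |
| 4 vs 4 months | 11–35% |
| 8 vs 8 months | 4–45% |

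At a mean of 1 fall per year, the upper ends of rows 2, 3, 4 and 6 become 66%, 72%, 56% and 47%. The lowest value, 3%, needs 24 falls per year and no variation between patients; with gamma-Poisson counts that cell is 11–15%. With equal windows, about 2% is reached only near 60 falls per year (4 months) or 30 (8 months), again with identical rates in all patients.

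**5. Power at 35 per group, 22-point gap kept.** Power = Φ{[0.22 − 1.96·√(2p̄(1−p̄)/35)] / √([p₁(1−p₁) + p₂(1−p₂)]/35)}.

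- 10% vs 32%: (0.22 − 1.96·0.0974)/0.0937 = 0.31, power 62%
- 20% vs 42%: (0.22 − 1.96·0.1106)/0.1074 = 0.03, power 51%
- 30% vs 52%: (0.22 − 1.96·0.1176)/0.1146 = −0.09, power 46%

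For 80% power, these would need 53, 69 and 78 per group. With all 38 per group retained, the same formula gives 66%, 55% and 50%.

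**The case against.** The strongest reply is that the article never says a 12-month count is set against a 4- or 8-month count. The 12-month history is an eligibility rule, the baseline falls history has no stated look-back, and the analysis section speaks of incidence, which may mean a rate. The exact window may sit in a fuller document. This stands: a reader might infer that the mismatch is what the plan prescribes, but the text only leaves it open. It does not rescue the 2%, which looks too low on the annualised and equal-window readings as well.

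Other tempting readings also go too far.

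- **That 2% is unattainable.** It can occur if falls are very frequent.
- **That unchanged patients become responders at both time points through window length.** This holds only at 4 months.
- **That the article's background figure supplies the missing rate.** "Approximately 40–70% of people with PD fall each year" describes people with Parkinson's disease in general, not patients selected for a recent fall plus freezing or slow gait.
- **That the result would favour the intervention.** Chance responders arise in both randomised groups; the loss is power, not a directional bias.

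It is also fair to say that the 22-point gap at higher control rates is an illustration. It cannot hold on the raw 12- versus 4-month reading at most of the simulated rates, since any control response above 78% would put the intervention group above 100%. Finally, the stated primary outcome, the count after randomisation, needs no baseline comparison. That is correct, and it makes the fix easier.

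**Conclusion.** The point holds in this form. The responder that sizes the trial and feeds the logistic model has no fixed baseline window or time point, and its assumed 2% control response is not credible without justification. No effect at all yields 75–87% responders on the raw 4-month reading, 21–63% on the raw 8-month reading, and roughly 3–67% once windows are annualised or matched. The active fall prevention given to controls could raise their response further.

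The stated 80% power depends on that input. At control response of 10–30% with the same gap it is about 62% down to 46%. These sizes rest on assumed fall rates of 1.2–24 per year, Poisson or gamma-Poisson counts, a two-sided 5% test and a retained 22-point difference.

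This is more than omitted detail, because a stated power rests on a number at odds with the plan's own eligibility rule and outcome. The sample-size arithmetic is not at fault.

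**What to change.** 1. Make the between-group comparison of the follow-up fall count the main falls analysis in place of the 50% responder model, for example by negative binomial regression with exposure time as offset and baseline falls as a covariate. This uses the primary outcome as already stated.
2. If a responder analysis is kept, define it on fall rates, state the baseline and follow-up windows, and name one time point.
3. Justify or replace the 2%, and restate the power at 70 and 76 patients over a range of control values. The trial need not be enlarged.

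The cost is a less favourable stated power and modest changes to the analysis text. The abstract describes the trial as ongoing, so matched pre-randomisation windows may not be recoverable for patients already enrolled if their falls were not dated. That is the reason to prefer the covariate approach, which can use whatever baseline history was recorded, provided it was recorded the same way in both groups.

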### Outcome measures

The study’s primary outcome measure will be the total number of falls in the 4-month (short-term benefit) and 8-month (long-term benefit) after randomization. A fall will be defined as unintentionally coming to rest on the ground or other lower surface without overwhelming external force or a major internal event [56].

Other secondary outcome measures will include: 1) Cost-effectiveness, which will be estimated using natural units of health outcomes, including the incremental cost-effectiveness ratio per fall prevented and cost per extra person avoiding mobility deterioration (identified as an average number of daily steps assessed by wearable sensors); 2) A cost-utility analysis using the EuroQoL will estimate the incremental cost per quality-adjusted life-years (QALY) gain; 3) Short and long-term rate of change from baseline to four and eight months, respectively of motor, NMS, gait, balance, HR-QoL, caregiver burden, and comorbidities severity; 4) Feasibility (completed telemedicine visits) and adherence (dropout rate of telemedicine visits).

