### Specific goals

The first objectives of this study are to study and compare the intervention vs. the control group, in terms of 1) the reduction of fall incidence (total number of falls from baseline) with the implementation of an additional multidisciplinary telemedicine program; and 2) the cost-effectiveness of this telemedicine program compared to usual care. Secondary objectives are: 1) to study the feasibility and patients’ adherence to new technology (defined as patients retention > 80% during the study), 2) to study the clinical utility of using wearable sensors to monitor gait dysfunction and physical activity, 3) to analyze the duration of clinical benefits after finishing a telemedicine program (short-term vs. long-term benefits), and 5) to develop a full-stack using Big Data frameworks that facilitate communication between the patient and the occupational therapist using Artificial Intelligence (AI) techniques.

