## Procedure

After signing the informed consent form, investigators will invite PD patients to participate in this randomized controlled trial. Patients will be randomly assigned using a block gender-randomization Excel calculator [male/female: intervention/control groups), providing an equal number of males and females with PD in the control/intervention groups (1:1). There will be no personal expenses for the participant during the study; instead, all assessments will be free, including the neurologist, nurse, psychologist, and occupational therapist evaluations. The patients will be contacted by phone to confirm they attended the treatment sessions. Likewise, reports of the assessments performed during the study will be available to improve patient adherence to the intervention protocols.

Two study phases will be established (Fig 1). In the *first phase* (baseline-4^th^ month), short-term benefits will be assessed. All participants will be evaluated at baseline and four months in office. Patients allocated in the intervention group will be receiving the telemedicine fall prevention program. The occupational therapist will bring the equipment for videoconferencing to the patients’ home, set up the room for physical therapy, and evaluate the patient’s risk of performing different exercises according to the patient’s capabilities and home environment. In the *second phase* (5^th^-8^th^month), long-term benefits will be assessed. All patients allocated in the intervention group will discontinue the telemedicine program at the end of the 4^th^ month. All patients will receive standard medical care provided by the movement disorder neurologist and nurse, with a final visit at eight months from baseline.

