### Statistical analysis

The study includes several necessary methodological resources that will minimize the risk of bias, such as the randomization process, allocation concealment, blinded assessment of the results, and intention-to-treat analysis. A statistician blinded to group allocation will supervise the data entry and analysis. The normality of the variables will be evaluated using the Kolmogorov-Smirnov test and graphs, including histograms and normal distribution plots. For the description of the quantitative variables, the mean and the standard deviation will be used, and for categorical variables, the frequency distribution and percentages. For non-normally-distributed variables, we will use the median, the interquartile range, and the corresponding non-parametric tests. The association between independent categorical variables will be analyzed using the χ2 test or Fisher’s exact test. The means between the two groups will be compared using the one-way analysis of variance (ANOVA). We will analyze the relationship between quantitative variables using correlation coefficients.

We will use logistic regression models to analyze the relationship between fall strategy prevention of 50% reduction in the incidence of falls (yes vs. no) as the dependent variable with the intervention vs. the control group, as the independent variable adjusted for age, gender, total motor MDS-UPDRS, comorbidity severity, and total levodopa equivalent dose. Other pertinent univariate and multivariable analyses will be performed based on the objective type. Also, given the complexity of potential analysis, including a diversity of variables from different origin and measurement properties, advanced statistical methodology (data mining, AI techniques) will be applied as needed. The level of significance will be set at p < 0.05. Statistical analysis will be performed with SPSS V.25.0. (IBM SPSS Statistics for Windows, Armonk, NY, USA).

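### The primary outcome is a raw total of falls, no stated analysis takes account of time observed, and the scoring of patients who leave early is left open

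*Protocol article*

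**What the plan says.** Under Outcome measures, the "primary outcome measure will be the total number of falls in the 4-month (short-term benefit) and 8-month (long-term benefit) after randomization". Under Specific goals, the first objective is "the reduction of fall incidence (total number of falls from baseline", so incidence is explained there as a total and not as a rate.

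Under Sample size, the design assumption is that "a 50% fall reduction in the number of falls compared to baseline will be obtained in 24% of the participants in the intervention group", against 2% of controls. The same paragraph continues: "By assuming a 9% dropout rate, a total sample of 76 patients will be then included in this study".

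Under Statistical analysis, intention-to-treat is listed among the protections against bias. The logistic model takes "fall strategy prevention of 50% reduction in the incidence of falls (yes vs. no) as the dependent variable", adjusted for age, gender, motor score, comorbidity and levodopa equivalent dose. Means are compared by ANOVA, or by non-parametric tests where normality fails. No rate, person-time term, offset or count model is named.

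Under Procedure, "All patients allocated in the intervention group will discontinue the telemedicine program at the end of the 4^th^ month", but all patients continue on standard care to a final visit at eight months. Under Specific goals, feasibility is met with any retention above 80%.

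**The concern.** A total over a fixed window is comparable between patients only if each is observed for the whole window. The protocol expects that some will not be, and it promises to analyse patients as randomised. It must therefore do something with partial counts, and the text as it stands offers two routes.

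- **Use the partial count unadjusted.** Less time observed means fewer falls recorded, so leaving early resembles improvement on the 50% criterion.
- **Leave these patients out.** The analysis is then of completers, which does not match the stated intention-to-treat principle.

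At stake is the primary comparison. It probably also affects the cost per fall prevented, which needs a fall count. A choice between the two routes made after the data are seen would be a post-hoc decision on the primary outcome.

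**Working it through.** **1. The protocol's own figure.** Inputs from Sample size: p1 = 0.24, p2 = 0.02, 5% type 1 error (two-sided assumed), 35 per group. Uncorrected normal formula with pooled variance under the null:

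z = [(p1 − p2)√n − 1.96·√(2p̄(1 − p̄))] / √(p1(1 − p1) + p2(1 − p2)), with p̄ = 0.13.

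- n = 35: (0.22 × 5.916 − 1.96 × 0.4756) / 0.4494 = 0.82, power 79.4%. For 80% power the formula needs 36 per arm, so the stated 35 is reproduced to within one patient per arm.
- n = 38 with no leavers: z = 0.94, power 82.7%.
- Dropout: 70/0.91 = 76.9 and 70 × 1.09 = 76.3, against 76 stated.

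**2. Does leaving early raise the chance of a nominal 50% reduction?** The protocol gives no fall rate, so the following are assumptions: Poisson falls, unchanged true rate, baseline and follow-up windows of equal length, at least one baseline fall. Simulated chance that the follow-up count is at most half the baseline count:

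| Mean falls per window | Full window | 75% observed | 50% observed | 25% observed |
|---|---|---|---|---|
| 1 | 53% | 63% | 74% | 86% |
| 4 | 23% | 38% | 59% | 83% |
| 8 | 11% | 28% | 56% | 87% |

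Overdispersed (gamma-mixed) counts behave the same way: 19% to 49% with the full window, 85% to 88% at a quarter of it. This shows the direction of the artefact only. The full-window values lie far above the 2% planned for controls, so they are not combined with that figure below.

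**3. Effect on the comparison when both arms lose patients equally.** Assume 9% of each arm leaves early and a share q of leavers is scored as responders. Then p1 = 0.91 × 0.24 + 0.09q and p2 = 0.91 × 0.02 + 0.09q, with 38 per arm:

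| q | Intervention | Control | Power |
|---|---|---|---|
| no leavers | 24.0% | 2.0% | 83% |
| 0.25 | 24.1% | 4.1% | 72% |
| 0.50 | 26.3% | 6.3% | 66% |
| 1.00 | 30.8% | 10.8% | 58% |

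**4. Effect when loss is unequal (q = 1, the extreme).**

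- 9% leavers in the intervention arm only: 30.8% vs 2.0%, power 94%.
- 9% leavers in the control arm only: 24.0% vs 10.8%, power 33%.
- No true effect (2% in both arms), 9% leavers in the intervention arm only: 10.8% vs 2.0%, about a 35% chance of p < 0.05. The normal approximation is rough at such low rates.

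**The case against.** The strongest reply is that no sentence in the protocol scores a leaver on a truncated count. A patient not followed to the end of a fixed window has no total for it, so the ordinary reading may be a missing outcome. Enlarging 70 to 76 points the same way, as does the rule under Ethical considerations that excludes the data of patients removed for discomfort. Missing-data detail often sits in an analysis plan that is not shown here. All of this stands against a stronger reading that a reader might infer, namely that the trial counts withdrawal as success. The documents do not say so.

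A reader might also infer that the end of the programme at month 4 builds in an exit at half of the eight-month window. That is not supported either. Procedure keeps every patient to the month-8 visit, and monthly sensor data are planned for all participants over the eight months. If the eight-month outcome means months 5 to 8 only, a patient who leaves at month 4 has no count for it, not half of one.

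The sizes, too, rest on assumed fall means, equal windows and a chosen share of leavers scored as responders. The 83% comparator is 38 per arm with no loss, whereas the protocol plans on 35 evaluable per arm.

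The reply does not remove the point. A total count, a glossed meaning of incidence and a covariate list without observed time are choices that the protocol makes. An analysis plan could add a scoring rule, but moving to a rate would alter the outcome as stated. The missing-outcome reading still leads to an analysis of completers.

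**Conclusion.** The point holds as a weakness in the chosen outcome and analysis. The protocol fixes a raw total, applies analyses that ignore time observed, expects 9% dropout and claims intention-to-treat; these do not fit together. The direction of bias is not fixed, because it depends on which arm loses more patients. With equal loss the contrast is diluted: in the illustration, power is 72% to 58%, against about 83% at 38 per arm with no leavers and about 79% at the planned 35 evaluable. With unequal loss an effect can be created or hidden. These figures assume that partial counts enter unadjusted and that 25% to 100% of leavers are scored as responders, neither of which the protocol states. It should be settled before the data are analysed, but it does not show that the trial's result will be biased.

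**What to change.** Under Outcome measures and Statistical analysis:

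- Analyse the number of falls with a count model, for example negative binomial, with the log of observed follow-up time as offset, including every randomised patient with any falls follow-up.
- Compute any 50% reduction on falls per observed month, for baseline and follow-up alike.
- Record the date of last falls information for each patient.
- Add a sensitivity analysis for incomplete follow-up, for example completers only, or leavers as non-responders. These are alternatives to the main analysis, not further rules within it.

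The cost is a little more analysis work and one form field. There are two limits. The offset assumes that a leaver's fall rate after leaving resembles the rate before, which is why the sensitivity analysis is needed. Individual rates over short follow-up are also imprecise: at an average of one fall per month under the Poisson assumption, a patient observed for one month has no falls with probability e⁻¹ = 37% and would still count as a responder. The count model should therefore carry the main comparison. Collecting falls by telephone from patients who miss a visit could help, but it would be a new procedure, since the calls now described only confirm attendance at treatment sessions.

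### The primary outcome is a fall count, but the sample size, the stated power and the only fall-specific model belong to a yes/no 50% reduction

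*Protocol article*

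**What the plan says.** All references are to the protocol article.

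- **Specific goals.** The first objective compares the groups on "the reduction of fall incidence (total number of falls from baseline", which is a count.
- **Outcome measures.** The "primary outcome measure will be the total number of falls in the 4-month (short-term benefit) and 8-month (long-term benefit) after randomization". This is again a count, at two time points, and neither is marked as the main one.
- **Sample size.** The calculation rests on "a 50% fall reduction in the number of falls compared to baseline", which "will be obtained in 24% of the participants in the intervention group and 2% in the control group". From this the section concludes that "70 patients (35 per group) would provide 80% power", and it adds 9% for dropout to reach 76.
- **Statistical analysis.** The only model that names falls is "logistic regression models to analyze the relationship between fall strategy prevention of 50% reduction in the incidence of falls (yes vs. no", with group as the independent variable. It adjusts for age, gender, motor MDS-UPDRS, comorbidity and levodopa equivalent dose. The section also lists one-way ANOVA for means, non-parametric tests for non-normal variables, and an open clause on other analyses. It ties none of these to the number of falls.

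**The concern.** Two sections define the primary outcome as one variable, and two others size and model another. A reader of the sample size section would take 80% to be the chance of detecting an effect on the primary outcome. It is the chance of detecting a difference in the proportion whose falls halve.

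The count, which is what the trial says it will report first, has no designated analysis. ANOVA, a rank test and the logistic model could each be presented afterwards as the primary result. ANOVA or a rank test on raw counts uses neither the length of follow-up nor each patient's earlier falls. The responder treats a change from 20 falls to 11 as failure and from 1 to 0 as success, so the two endpoints can rank patients, and treatments, differently.

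**Working it through.** **1. Does the stated sample size belong to the responder?** Inputs from Sample size: p₁ = 0.24, p₂ = 0.02, α = 0.05 (taken as two-sided, since sidedness is not stated), power 0.80.

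n per arm = [1.960·√(2·p̄·(1−p̄)) + 0.842·√(p₁(1−p₁) + p₂(1−p₂))]² / (p₁−p₂)², with p̄ = 0.13

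= [1.960·√0.2262 + 0.842·√0.2020]² / 0.22² = (0.932 + 0.378)² / 0.0484 = 35.5, so 36 against 35 stated.

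Power at 35: Φ[(0.22·√35 − 0.932) / 0.449] = Φ(0.82) = 79.4%. Dropout: 70/0.91 = 76.9, against 76 stated. The figures reproduce within rounding, so the sizing rests wholly on the responder.

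**2. What power does 35 per arm give for the count?** The article gives no fall rate, dispersion or rate ratio, so these are assumptions: control mean μ = 1, 2 or 4 falls in 4 months, and dispersion k = 0.5, 1 or 2. For a negative binomial comparison without baseline adjustment:

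n per arm = (1.960 + 0.842)²·(1/μ + 1/(μ·RR) + 2k) / (ln RR)²

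Example with μ = 2, k = 1, RR = 0.5: 7.849 × (0.5 + 1 + 2) / 0.4805 = 57.2, so 58. Power at 35 = Φ(0.693/√(3.5/35) − 1.960) = Φ(0.23) = 59%.

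n per arm for 80% power at RR 0.5 (power with 35 per arm in brackets):

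| μ | k = 0.5 | k = 1 | k = 2 |
|---|---|---|---|
| 1 | 66 (54%) | 82 (45%) | 115 (34%) |
| 2 | 41 (74%) | 58 (59%) | 90 (42%) |
| 4 | 29 (87%) | 45 (70%) | 78 (47%) |

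At RR 0.7 the same grid needs 100–397 per arm, and 35 per arm gives 13–38% power. Solving the formula for RR with 38 per arm and complete follow-up gives a detectable ratio between 0.26 (μ = 1, k = 2) and 0.55 (μ = 4, k = 0.5). Check at μ = 2, k = 1, RR = 0.417: 7.849 × (0.5 + 1.199 + 2) / 0.765 = 38.

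**3. What does a count model with baseline falls gain?** Simulation with 35 per arm, RR 0.5 over 4 months, gamma-Poisson falls with dispersion 1, and every patient having at least one fall in the prior year. The responder is defined as a 4-month fall rate at most half the prior-year rate. Power in %:

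| Mean prior-year falls | 4 | 8 | 16 |
|---|---|---|---|
| Stable individual rates: negative binomial with log baseline falls | 78 | 96 | 99 |
| Responder test | 51 | 74 | 88 |
| Rank test on counts | 52 | 64 | 70 |
| Drifting individual rates: negative binomial with log baseline falls | 56 | 71 | 81 |
| Responder test | 38 | 42 | 54 |
| Rank test on counts | 36 | 44 | 42 |

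Type I error of the negative binomial test was 4–6%. A repeat with 300 trials per cell, and drift as a gamma multiplier of mean 1 and variance 0.5, gave 61/73/85 for the negative binomial against 39/43/53 for the responder, so the drift figures hold within a few points. A further 1,500 null trials per stable-rate scenario, with a Poisson fallback where no overdispersion remained, gave type I error of 5–6%.

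**4. How much of that gain comes from the count itself?** In a second simulation over the μ and k grid of step 2, at RR 0.5 and 0.7, the efficiency of the responder test was 0.38–0.61 relative to the baseline-adjusted negative binomial model, but 0.60–1.31 relative to the unadjusted one. Much of the gain therefore comes from using baseline falls.

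**The case against.** Four readings stronger than the text supports are tempting.

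- **Dichotomising discards most of the information.** A reader might infer this, but it cannot be shown. The article gives no fall rate or dispersion, and step 4 puts the loss at 39–62% against a baseline-adjusted model, and anywhere from 40% to nothing against an unadjusted one. The responder is defined against each patient's own baseline, so it already uses some of that information.
- **The count has no test at all.** It does: the generic non-parametric tests can be applied to it, and a rank test is a valid comparison. What is lacking is a designated analysis. A full protocol or analysis plan could supply model details, so the absence of an offset or a covariate list is not itself the finding.
- **The sample size is miscalculated.** It is not; step 1 reproduces it.
- **Cost per fall prevented needs a rate ratio.** It needs a difference in mean falls, which both arms supply whatever test is used.

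The simulation is also not calibrated to this trial. With stable rates its responder proportions are about 21–42% in controls and 59–66% under treatment, far from the planned 2% and 24%. Its power for the responder test therefore does not replace the 79.4% on the planned inputs. It shows an ordering, which held in all six scenarios, and not a forecast.

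Finally, the contradiction could be removed the other way, by naming the responder as primary. That would match the existing sample size. On the planned proportions, however, it leaves 35 × 0.24 + 35 × 0.02 = 9.1 expected responders for a logistic model with group and five covariates. The chance of no control responder is 0.98³⁵ = 49%, in which case the ordinary odds ratio for group cannot be estimated.

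**Conclusion.** The mismatch stands and needs only the article's own text: Specific goals and Outcome measures name a fall count, while Sample size and the logistic model use a 50% responder. The stated 80% power belongs to the responder. Power for the named outcome is given nowhere, and no analysis of it is designated.

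The mismatch is certain; its cost in power depends on assumptions. At a true rate ratio of 0.5, 35 per arm gives 34–87% for an unadjusted count comparison across the assumed fall rates and dispersions. At dispersion 1, adjusting for baseline falls gives about 78–99% with stable individual rates, against 51–88% for the responder test, and about 56–81% against 38–54% if rates drift. The detectable effect on the count may therefore be less favourable than the stated 80% suggests.

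**What to change.** 1. Keep the fall count as primary. Analyse it by negative binomial regression with log follow-up time as offset and group, gender and log baseline falls as terms, and report the fall rate ratio with its 95% CI. Entry requires at least one fall in the previous 12 months, so the log is defined if that is the baseline period; state the period.
2. Designate one time point, for example months 0–4, as primary. Analyse the 8-month count with the same model as a stated further analysis, so that it is not dropped silently.
3. Make the 50% responder secondary.
4. In Sample size, say that 70 and 76 patients and 80% power were computed for the responder. Add the rate ratio detectable with 76 under an explicitly assumed fall rate and dispersion.

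**Cost.** No new data are needed, since fall history is taken at every in-office visit. The text changes are small. Item 4 needs planning values that the article does not contain, and the resulting detectable effect may be large enough to put the planned number of patients in question.
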